***HIPAA***

Describe if data to be collected contain any protected health information (PHI) and specify which PHI is to be collected. Health information is determined to be PHI if it contains any of the following identifiers:

| - Name, address, telephone number, date of birth - Personal and family medical history - Current and past medications or therapies - Hospitalization & other institutional care information | - Information from a physical examination that generally also includes blood pressure reading, heart rate, breathing rate and temperature - Results of tests and procedures you will undergo during this research study as described in the informed consent form. |  |
| --- | --- | --- |

Data will be stored in locked file cabinets and in password protected files behind firewalls. Only staff with appropriate training to ensure that privacy is protected according to HIPAA and human subjects’ protection programs will be allowed access to participant data.

***5. Tissue Specimens***

Blood will be obtained at baseline and six-months.

The specimens:

- Were not collected during regular clinical care
- Would not have otherwise been discarded
- Are not publicly available
- Are collected as part of the research protocol
- This research involves banking of blood for future uses

***6. Genetic Testing***

Not applicable

**RISK/BENEFIT ASSESSMENT**

***1. Potential Study Risks***

**Likely (greater than 20%)**

- Muscle or joint soreness or injury from the maximal exercise test or exercise training. These are usually mild, last a week or less, and require little medical attention, if any. The types of injuries that are most common from aerobic exercise such as what you will do in the exercise test or training are hip, knee, ankle, or foot joint pain, or muscle aches. Sometimes these injuries are mild enough that you will not need to seek any medical attention and your daily activities will not be altered. It is estimated that over any given month, 4% of adults who walk for exercise on a regular basis will incur an injury severe enough to cause a change in activities of daily living for a week or more and that require medical attention. These injuries are rarely serious in nature and generally resolve with reduced activity and greater attention to appropriate footwear, gradual increase in training intensity, and adequate stretching.
- Mild abrasions and stinging at the site where we clean the skin for the electrodes for the treadmill test.
- DEXA scan risks:
  - You will receive a radiation dose. This radiation dose is not necessary for your medical care and will occur only as a result of your participation in the study.
  - At doses much higher than you will receive, radiation is known to increase the risk of developing cancer after many years. At the doses you will receive, it is very likely that you will see no effects at all.

**Less Likely (Less than 20%)**

- The potential for embarrassment at having weight measured or answering specific survey questions
- There is a small risk of infection when your blood is being taken, but the risk is minimal as all needles and equipment are sterilized and the procedures are performed by a trained professional. You may experience some mild to moderate pain lasting a few seconds upon insertion of the needle used to draw the blood. You may also get a bruise from the blood draw.
- Some personal health information could be revealed, despite efforts to avoid this.

**Serious but rare (Less than 2–3%)**

- 6-minute walk test risks. The risk of cardiovascular events from the six minute walk test is less than 1 in 5000. This test will be performed within the Exercise Medicine Unit at the Presbyterian Hospital location of the Clinical and Translational Research Center. Individuals for whom participating in this test is unsafe will be excluded from participation in the study.

***2. Potential Study Benefits***

**Potential Benefits to Subjects:** Participants in the exercise groups are expected to experience improved cardiorespiratory function, and improved quality of life. All participants will receive a treadmill delivered and set up in their home for no charge to them. Participants randomized to the exercise group will receive their treadmill at the beginning of the study. Participants randomized to the control group will receive their treadmill after completing the study. There may be benefits to their cell adhesion and circulating tumor cell function as well.

**Potential Benefits to Others:** Regardless of whether the hypotheses regarding the mechanisms of colon cancer recurrence are supported, this work will improve our knowledge of the feasibility, safety, and the benefits of two distinct doses of aerobic exercise on quality of life and functional well-being among colon cancer survivors.

**Importance of the Knowledge to be Gained:** If the primary hypothesis of this study is supported, this will support the further exploration of the dose response effects of exercise for reducing the risk of recurrence in colon cancer. If the secondary hypotheses are supported, this trial will increase confidence in the potential for exercise to improve long-term outcomes among colon cancer including cancer-specific and overall survival. If our hypotheses are not supported, this study will improve our knowledge about exercise prescription in this population. Upon study completion, the investigators will summarize the major findings of the study, such as feasibility of exercise, and notify all study subjects via a mailed letter. The purpose of this letter will be to thank study subjects for their participation and to inform them of the findings of the study.

***3. Alternatives to Participation***

The participants recruited would have the option of paying for a gym membership at a facility with fitness professionals who are trained in teaching a progressive aerobic exercise protocol for CC cancer survivors.

***4. Data and Safety Monitoring***

**Introduction**

Since this study constitutes a clinical trial, although we are not study experimental drugs, the intervention is experimental with the attendant risks described above in the Human Subjects section. Therefore it is appropriate to have a Data and Safety Monitoring Plan (DSMP) to monitor the study with an attendant monitoring plan as outlined below.

Every effort will be made to report an event as a diagnosis, not as a list of symptoms. Symptoms that led to the diagnosis should be included in the event description, but should not be the actual event.

Once an event is reported, you must keep the information accurate and current in Velos. If new/updated information is learned about the event, the event should be amended or corrected promptly.

Only an investigator may determine the grade, attribution and expectedness.

NOTE: The DSMC reserves the right to modify the reporting requirements for studies of specific interest.

On-Site subjects (this includes any subjects enrolled at other sites on an in-house study)

1. All grade 3 or higher events (AE or SAE) within five business days of knowledge.
2. All unexpected deaths within 24 hours of knowledge.
3. All others deaths within 30 days of knowledge. Deaths of subjects off-study for greater than 30 days from the last study treatment/intervention are not reportable with the following exceptions:
4. Deaths on in-house gene or cellular-therapies
5. Deaths on in-house studies utilizing on-campus manufacturing of the study agent(s) or components of the study agent(s)
6. Deaths on first-in-human studies

Off-site (external sponsors)

1. All SAEs (on the specific protocol opened here only) defined as reportable in the protocol for Phase I and II studies.
2. SAEs on cooperative or industry sponsored Phase III studies do not have to be reported.
3. SAEs on consortium or foundation sponsored (not just funded) Phase III have to be reported if the protocol defines them as reportable.
4. All deaths on first-in-human studies, must be reported at the time the event is reported to the sponsor.

We will establish a comprehensive plan to monitor the data and safety of the human participants in this trial. The PI, [name], will ultimately be responsible for ongoing on continuous monitoring of the safety of the human participants in the trial, as guided by the DSMP. The proposed study aims to determine the effects of varying doses of moderate-intensity aerobic exercise on various biomarkers among a clinical population with colon cancer. The intervention protocol poses minimal risks to participants. Because of this risk status, the DSMP for this trial focuses on monitoring by the principal investigator and biostatistician, along with prompt reporting of excessive adverse events and any serious adverse events to the NIH, the IRB, the University of Pennsylvania’s Abramson Cancer Center Clinical Trials Scientific Review and Monitoring Committee (CTSRMC).

Who will monitor this study? Check all that apply.

Principal Investigator

Sponsor or contract research organization

NCI sponsored cooperative group

Cancer Center (if mandated by CTSMRC)

Medical monitor

Safety monitoring committee

Data and safety monitoring board

**DSMP reports**

DSMP reports will be produced by the study coordinator. We will adapt adverse event reporting forms from our prior ongoing and completed study for this study. Safety reports will be sent to the study statistician and the PI. The project coordinator will be responsible for assembling the data and producing these reports, as well as assuring that all parties obtain copies of these reports. The frequency of data review for this study is summarized below:

| Data Type | Frequency of Review |
| --- | --- |
| Subject accrual (adherence to protocol regarding demographics, inclusion/exclusion) | Quarterly |
| Adverse event rates (injuries, symptom changes requiring altered exercise prescription) | Quarterly |
| Compliance to treatment, dropout rates | Monthly |

**Responsibilities of the PI and Statistician**

The PI and statistician will meet once before subjects are accrued into the trial to review safety protocols and stopping rules and ensure that the procedures for stopping the trial early are clear and empirically based. Thereafter, the PI and statistician will meet quarterly to review subject accrual, adverse event rates, stopping rules report, and compliance to the intervention. If there is any interim concern between these meetings, they will be handled via email as much as possible. A checklist will be developed and used to determine whether any corrective action is needed at any particular time during the study. The PI and statistician will be allowed to trigger an ad hoc review at any time. Stopping rule violations will be avoided by these actions, but if they should occur, they will be communicated to the NIH and to the IRB. In addition, the PI and statistician may comment on whether the study investigator needs to report any specific out of range measurement results to a participant and/or his/her physician.

**Measurement and reporting of subject accrual, adherence to inclusion/exclusion criteria**

Review of the rate of accrual, and adherence to inclusion and exclusion criteria will occur quarterly during the recruitment phase. Review to assure that participants meet eligibility criteria and ethnic diversity goals outlined in the grant proposal will occur quarterly during the recruitment phase.

**Measurement and reporting of adverse events**

Adverse events will be collected as they occur. Musculoskeletal injuries and previously undocumented major medial events incurred during the intervention will be systematically collected on all participants at the final six month study visit using standardized forms from our prior work. The adverse event form will be used by study staff to report injuries or other adverse events reported by participants throughout the study.

**Stopping rules**

**Stopping rules regarding injuries from exercise training**

There is some level of injury expected from exercise training. The PI and study statistician will review exercise training injury rates quarterly. If the rate of injuries attributed to exercise and lasting a week or longer is more than 4-fold higher over 3 months among treatment than control group participants, it will be reported to the NIH, the IRB, the University of Pennsylvania’s Abramson Cancer Center Clinical Trials Scientific Review and Monitoring Committee (CTSRMC). Most exercise training injuries are mild in nature, and allow a complete return to the same activities after slowing reintroducing the exercise that caused the injury. Another approach is to substitute a different mode of exercise that does not place excessive demand on injured muscle, tendon, ligament, or other soft tissue fibers.

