**OBJECTIVES**

***1. Overall Objectives***

We will compare the feasibility and safety of two doses of aerobic exercise among 39 CC survivors, while simultaneously exploring the potential biological effects. We aim to compare 150 min∙wk^-1^ and 300 min∙wk^-1^ of moderate-intensity aerobic exercise to a wait-list control group. The findings from this study will help to establish the feasibility and safety of the dose-response effects of exercise among CC survivors and provide effect size estimates to inform the development of a phase III trial.

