
**Colon Cancer and Physical Activity**. Increasing levels of post-diagnosis physical activity (PA) are associated with a 42% improvement in disease-free survival,[24] 40% reduction in cancer recurrence,[24] and 45-71% reduction in CC-specific mortality.[24-26] The evidence also suggests PA improves outcomes in dose-response fashion, such that CC survivors who engage in larger volumes of PA have more favorable disease free survival (p_trend_=0.01), recurrence (p_trend_=0.03), and CC-specific mortality (p_trend_=0.008).[24-26] The relationship between PA volume and CC outcomes has been depicted as a linear or quadratic pattern using smoothed splines.[24,26] The splines suggest 225 min∙wk^-1^ may be the minimum threshold necessary to improve CC outcomes, as is prescribed in current ongoing studies.[81,82] However CC outcomes continue to improve beyond 225 min∙wk^-1^, suggesting that larger doses may be more efficacious.[24,26] PA volume >400 min∙wk^-1^ does not appear to confer additional improvements in these outcomes. Categorically, a dose of ~300 min∙wk^-1^ of moderate-intensity PA appears necessary to reduce recurrence, improve disease-free survival, and improve CC-specific mortality.[24-26] It remains unknown if larger doses of exercise are behaviorally feasible and have tolerable safety and symptom profiles.[24] Interestingly, levels of PA before diagnosis of CC do not associate with CC-specific mortality.[25,61,83] This suggests the hypothesized pathways in which PA associate with primary prevention of CC may differ from that of secondary prevention of CC.[84] The American College of Sports Medicine (ACSM) and the American Cancer Society published guidelines for cancer survivors, recommending 150 min∙wk^-1^ of moderate intensity PA.[85,86] This recommendation is inconsistent with the dose of PA necessary to reduce recurrence, and improve CC-specific mortality indicated by the epidemiologic literature. Several reviews, including The ACSM statement for exercise among cancer survivors, have called for more research to empirically investigate the dose-response effects of exercise,[86-89] and the safety profile of prescribing larger doses of exercise.[86,90] Among 295 breast cancer survivors who participated in our PAL trial,[91,92] a yearlong weight-lifting study, 21% required a dose-modification or cessation of weight-lifting as a result of a health event.[93] These findings parallel evidence from adults aged ≥70 years in an exercise trial, where 34% of participants had a healthcare event that influenced their completion of the initial prescribed dose of exercise.[94] The insufficient evidence regarding the specific dose of exercise necessary to improve CC outcomes likely serves as a barrier to the dissemination of exercise to CC survivors. Clinicians have noted they do not know what tell their patients about exercise.[95] The majority of clinicians (57%) provide no recommendation about PA.[96,97] Obtaining systematic data pertaining to dose-reduction or cessation of exercise is critical to future optimization of the allocation of behaviorally intensive resources, such as cancer rehabilitation and exercise programming. These data may be fruitful as exercise moves towards the forefront for consideration as a standard of care for cancer survivors, similar to cardiac rehabilitation.[96]

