**Medical record abstraction.** Medical characteristics such as tumor pathology, surgical history, chemotherapy treatment plan, laboratory tests, and any prior comorbid conditions will be extracted from pathology reports and/or the electronic medical record implemented in all practices at the University of Pennsylvania. This data will be collected for all potentially eligible study participants.

**Randomization.** After completion of the eligibility screening and baseline measurements, participants will be randomized evenly to one of three study arms. Randomization will be stratified by stage of cancer (stage II vs. III). Participants will be randomized by the study coordinator using electronic randomization

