***2. Statistical Analysis***

**Primary Outcomes**

We will randomize 13 participants to each of the three study arms (control, 150 min∙wk^-1^, 300 min∙wk^-1^), to achieve 10 per group who complete the study (76% completion rate). Participants who have a cancer recurrence during the study will be excluded from the primary outcome analysis. The sample size is powered for the primary outcome biomarkers (sICAM-1 and sVICAM-1) with a hypothesis for a linear trend. The standard deviation of sICAM-1 and sVCAM-1 are 30 and 103 units, respectively. Against the hypothesis of a dose-response relationship with decreases of 22 and 44 units for low- and high-dose respectively for sICAM-1 and 74 and 148 units for sVCAM-1, 30 subjects provide 80% power for two, two-sided 0.025 tests (one for sICAM-1 and one for sVCAM-1, with the Type I error adjusted to maintain the experiment-wise error rate of 0.05). These reductions are consistent with prior exercise interventions in non-cancer survivorship populations, where clinically significant reductions in sICAM-1 and sVCAM-1 occur with 30 and 75 unit changes, respectively.[99-103]

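### The injury reporting trigger does not say which exercise arms it compares with control; read plainly it pools the two doses, so an excess confined to the 300 min/wk arm is diluted

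*Protocol*

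**What the plan says.** The trigger is in the Protocol, Risk/Benefit Assessment, section 4 (Data and Safety Monitoring), under the stopping rules for exercise injuries. It counts "the rate of injuries attributed to exercise and lasting a week or longer" and requires a report to the NIH, the IRB and the cancer center's monitoring committee when that rate is "more than 4-fold higher over 3 months among treatment than control group participants". On frequency it says: "The PI and study statistician will review exercise training injury rates quarterly". Crossing the threshold leads to a report; it does not stop the trial.

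There are two exercise arms and one control arm. Under Statistical Analysis, Primary Outcomes: "We will randomize 13 participants to each of the three study arms". Under Study Procedures, Randomization: "participants will be randomized evenly to one of three study arms".

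The Overall Objectives state the purpose: "We will compare the feasibility and safety of two doses of aerobic exercise among 39 CC survivors". The Background says of the higher volume: "It remains unknown if larger doses of exercise are behaviorally feasible and have tolerable safety and symptom profiles".

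No part of the Data and Safety Monitoring section sets an injury threshold by arm. The review table under DSMP reports lists adverse event rates quarterly, including injuries, and does not say whether they are shown by arm or pooled.

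**The concern.** The trial asks whether the larger dose is as safe as the smaller one, but the one fixed rule that watches injuries during the trial contrasts exercise as a whole with no exercise. If the harm lies mainly in the 300 min/wk arm, averaging it with the 150 min/wk arm weakens the signal before it meets the 4-fold threshold.

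At stake is external notice of injuries that last a week or longer but fall below grade 3. For these the trigger is the only route with a number attached. A later statistical analysis plan would not obviously repair this, because the rule operates during conduct and is fixed in the protocol.

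**Working it through.** **Inputs from the Protocol.** Threshold: rate ratio above 4 over 3 months (stopping rules). Allocation 1:1:1, 13 per arm (Randomization; Primary Outcomes). Accrual of 39 participants over 15 months (Accrual). Intervention of 26 weeks, about 6 months (Table 1). Injury rate of 4% per month in adults who walk regularly for exercise (Potential Study Risks).

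**Assumptions.** Pooled reading of the word treatment. Control injury rate of 1% to 4% per month: the protocol gives no rate for controls, and 4% is a high value for people asked to keep their usual activity. Poisson counts. If control has no injury in the quarter, any exercise injury counts as exceeding the threshold.

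The 4-fold threshold is set, not derived, so there is no plan figure to reproduce.

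**Step 1: dilution.** With equal person-time the pooled rate is (r150 + r300)/2, and the trigger stays silent while this is at most 4c, where c is the control rate. Hence r300 ≤ 8c − r150.

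| 150 arm, multiple of control | 300 arm can reach, multiple of control |
|---|---|
| 0 | 8 |
| 1 | 7 |
| 2 | 6 |
| 3 | 5 |
| 4 | 4 |

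Compared separately, the 300 arm meets the trigger above 4 times control, whatever the 150 arm does. Seven also depends on person-time. If w is the 300 arm's share of exercise person-time and the 150 arm is at the control rate, the ceiling is (4 − (1 − w))/w: 8.5 at w = 0.4, 7 at 0.5, 6 at 0.6.

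**Step 2: person-time in one quarter.** If all 13 participants of an arm were present throughout, it would be 13 × 3 = 39 person-months per arm. Even accrual gives fewer: 39 × 6/15 = 15.6 people in the intervention at once, 5.2 per arm, so 5.2 × 3 = 15.6 person-months per arm.

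**Step 3: chance of firing in one quarter, 300 arm truly at 7 times control, 150 arm at control.** Pooled rule: injuries in the two exercise arms together exceed 8 times the control count. By-arm rule: either arm exceeds 4 times the control count.

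| Person-months per arm | Control rate per month | No control injury | Pooled | By arm |
|---|---|---|---|---|
| 39 | 4% | 21% | 53% | 77% |
| 39 | 2% | 46% | 52% | 70% |
| 39 | 1% | 68% | 65% | 68% |
| 15.6 | 4% | 54% | 55% | 68% |
| 15.6 | 1% | 86% | 61.0% | 61.1% |

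The third column is exp(−person-months × rate); the last row, for example, is exp(−0.156) = 0.856. In those quarters the two rules behave identically, which is why the gain disappears when control injuries are rare.

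**Step 4: cost in extra reports.** With no true excess in either arm, the chance of a report at 39 person-months and 4% per month is about 20% pooled and 21% by arm. At 15.6 person-months the two agree to within 0.1 percentage point (both 38% at 4% per month).

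**The case against.** **Pooling is inferred.** The rule does not define treatment, and the paragraph on participant compliance speaks of treatment groups in the plural. This stands: what is shown is unclear wording whose more natural reading is pooled. If a by-arm comparison was intended, the text still needs to say so.

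**Seven-fold is an extreme case.** It requires 150 min/wk of new walking to cause no more exercise-attributed injuries than usual activity, while the same section expects some injury from training. Both arms also follow the same progression in weeks 1 to 4. This stands too: seven is a conditional ceiling, and it falls as the 150 arm's rate rises.

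**Control injuries may often be zero.** Controls receive no study exercise, and only injuries attributed to exercise count. In such quarters pooling changes nothing. This limits the practical effect but does not remove it, and mending the zero-denominator weakness alone would leave the dilution in place.

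**Other routes exist.** Grade 3 or higher events are reported within five business days. The monitoring plan promises prompt reporting of excessive adverse events, the PI and statistician may call an ad hoc review, and the safety report has an open section for other concerns. A reader might therefore infer too much in saying that a high-dose injury excess would be reported late or never; the documents do not support that. Except for grade 3 events, though, these routes are discretionary or carry no number.

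**The report may already be by arm.** A reader might also infer that the quarterly report could not show which dose produced a signal. The protocol does not say that the report pools the arms, and its analysis compares dose reduction or cessation in each group. That inference fails.

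**Pooling 26 against 13 is defensible in a small pilot**, since splitting shrinks the denominators. Fair, but the threshold leads only to a report, and Step 4 shows that splitting adds few of them.

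**Conclusion.** The point holds in limited form. The protocol's only numerical injury trigger does not name the arms it compares, and its plain reading averages over the dose contrast that the trial sets out to examine. Given equal person-time and a 150 arm at the control rate, the 300 arm can reach 7 times the control rate without meeting this trigger.

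The practical loss ranges from 24 percentage points in the chance of firing per quarter (39 person-months per arm, 4% per month), through 13 points at the person-time that even accrual implies (15.6, 4%), to none (15.6, 1%). These figures rest on an assumed control rate and on Poisson counts. Examples that place all 13 participants of each arm in the same quarter are tempting but do not fit 15-month accrual, so the 39 person-month rows are an upper bound.

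The gap concerns injuries below grade 3 that last a week or longer. It is a modest weakness in safety monitoring and does not show that harm would go unseen.

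**What to change.** In the stopping rule for exercise injuries, state that the existing comparison is made for each exercise arm separately against control (150 min/wk against control, and 300 min/wk against control). The sponsor's threshold, time window and reporting recipients stay as they are. Under DSMP reports, require injuries and person-time to be shown for each of the three arms every quarter.

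The cost is one sentence and a few columns in a report that is already produced. The downside is smaller denominators and an occasional extra report. If the sponsor prefers to keep the pooled comparison, the text should say so explicitly and still show the by-arm counts.
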